#### Economic evaluation/ analysis

The valuation of resource use will be based on the valuation rates by Bock et al. [49]. The costs of the intervention include the training time and supervision of day-care centre staff, and materials (manuals, handbooks, etc.)., To analyse cost difference between groups, a multivariable model with a gamma distribution will be used to account for the skewed distribution of the data [50], adjusted for baseline costs. A 95-% confidence interval for the adjusted cost difference will be estimated from 1000 bootstrap replications. A cost-utility analysis from a societal perspective will be performed in which the quality of life of both day-care users and informal caregivers will be assessed. To calculate the quality-adjusted life years for day-care users regarding the time remaining at home, the quality of life values will be set to 0 from the day of admission to a nursing home or death. Moreover, a budget impact analysis will be computed to address changes in the expenses of the health care system if the MAKS therapy shows significant effects.

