#### Brief telephone intervention for informal caregivers

In addition to the MAKS therapy provided by the day-care centres, all caregivers in the intervention group receive three brief outreach telephone interventions. The task of the counsellors is to support the caregivers through three manualised phone calls, each lasting roughly 1 h. The goal is to work with the caregivers to develop strategies for self-management, to reduce the stress involved in providing home care, and to deal with challenging behaviours in order to “empower” the caregivers by improving their skills. The intervention includes tried and tested procedures from stress psychology, adjusted to fit the informal caregivers’ situations. Specifically, elements of the following procedures are employed: stress inoculation training as described by Meichenbaum [29], time structuring for the day, selection and prioritisation of goals, and development of positive activities. The procedure follows the self-management approach [30], that is, the aim is to enable the caregivers to use the strategies they have learned as fast as possible and to apply them in a beneficial manner.

“Challenging behaviours”, which occur in dementia in particular, are frequently experienced as especially stressful by caregivers. The intervention therefore includes information on the reasons for behaviour that is outside of the norm and the teaching of strategies that can be applied to reduce the occurrence of challenging behaviours, especially including references to the established Need-Driven Behaviour model to understand challenging behaviour [31, 32]. The counsellor’s basic attitude is client-centred [33] and solution-oriented.

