The phone calls are made at the beginning of the 6-month intervention phase, after about 2 months, and towards the end of the intervention phase. The intervention is carried out by two counsellors with training in psychotherapy who were given special training beforehand and regular supervision. The first phone call begins by determining the specific stress triggers and the behaviours that the caregiver identifies as challenging, followed by an explanation of some initial possible coping modes and information about the challenging behaviours the caregiver has experienced. The telephone counsellors help the informal caregivers develop concrete changes in their own behaviour. When necessary, the counsellors suggest that the caregiver might wish to take advantage of support services in their area. In the second phone call, the behaviour changes proposed in the first phone call and their effects are discussed. The third phone call serves as a booster session and is made towards the end of the 6-month intervention phase. Jointly developed “homework” tasks are intended to support learning and to help caregivers work on their issues during the periods between the phone calls.

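### The only user QALY described scores nursing-home residents as 0, like the dead, so it measures quality-weighted time at home; the listed costs also do not name the telephone counselling

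*Protocol article*

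**What the plan says.** Two statements in the protocol article, section Economic evaluation/ analysis, matter here.

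The first fixes the utility of day-care users. It opens "To calculate the quality-adjusted life years for day-care users regarding the time remaining at home" and continues that "the quality of life values will be set to 0 from the day of admission to a nursing home or death". No other QALY for users is described, and no sensitivity analysis on this rule is mentioned. The sentence just before introduces the analysis that it serves, in which quality of life is to be measured in both members of the dyad: "A cost-utility analysis from a societal perspective will be performed in which the quality of life of both day-care users and informal caregivers will be".

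The second lists costs: "The costs of the intervention include the training time and supervision of day-care centre staff, and materials (manuals, handbooks, etc" and so on. The section Brief telephone intervention for informal caregivers describes a further part of the intervention: "all caregivers in the intervention group receive three brief outreach telephone interventions". These are "three manualised phone calls, each lasting roughly 1 h", delivered by "two counsellors with training in psychotherapy who were given special training beforehand and regular supervision". The counselling is not among the cost items named.

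**The concern.** On the QALY scale 0 is the value of being dead. Giving it to someone who is alive in a nursing home turns the measure into time at home weighted by quality. That quantity is legitimate in itself, but it is not what a societal cost-utility analysis divides costs by.

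The choice touches the trial's own question. Hypothesis iii is that users stay in home care longer and that an economic advantage follows. Under the rule each day of postponed admission earns the full at-home utility, although the real gain is only the difference between living at home and living in a nursing home. The Background also reports that MAKS worked in nursing homes; a benefit that lasted beyond admission could never produce a QALY under this rule.

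On costs, caregiver quality of life is to be counted while the component aimed most directly at caregivers does not appear in the cost list. If the list were applied as printed, cost in the intervention arm alone would be understated.

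**Working it through.** The article gives no numerical result for this analysis, so there is no figure to reproduce.

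**Inputs from the article.** Utility 0 from admission (Economic evaluation/ analysis); 453 dyads (Eligibility of participants, Caregivers); three calls of about 1 h per intervention-group caregiver (Brief telephone intervention for informal caregivers); 34 centres, with four intervention centres described as 24% of that arm (Data quality management).

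**Assumed, because the article does not give them.** Utility at home 0.5 to 0.7; utility in a nursing home 0.2 to 0.6; difference in mean time at home −30 to +90 days; counsellor rate EUR 30 to 100 per hour. Survival is taken as equal in both arms.

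**Step 1: effect of the zero rule.** Let d be the difference between arms (intervention minus control) in mean days at home, offset by days in a nursing home.

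- Rule as written: u_home × d/365
- Nursing-home time valued: (u_home − u_nh) × d/365
- Excess: u_nh × d/365, which has the sign of d
- Ratio: u_home/(u_home − u_nh), which does not depend on d

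| u_home | u_nh | d (days) | Rule as written | Nursing-home time valued | Ratio |
|---|---|---|---|---|---|
| 0.6 | 0.2 | +90 | 0.148 | 0.099 | 1.5 |
| 0.6 | 0.4 | +90 | 0.148 | 0.049 | 3 |
| 0.6 | 0.6 | +90 | 0.148 | 0 | no limit |
| 0.6 | 0.4 | 0 | 0 | 0 | none |
| 0.6 | 0.4 | −30 | −0.049 | −0.016 | 3 |
| 0.7 | 0.2 | +90 | 0.173 | 0.123 | 1.4 |
| 0.5 | 0.4 | +90 | 0.123 | 0.025 | 5 |

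A mean difference of 90 days across all users is large. For a smaller case, assume 20% v 15% admitted evenly over 24 months and alive to the end. Each person admitted then spends 1 year on average in a nursing home, so d = 0.05 × 1 year = 0.05 year. With u_home = 0.6 the rule gives 0.6 × 0.05 = 0.030 QALY. Valued at u_nh = 0.4 the gain is 0.2 × 0.05 = 0.010; at u_nh = 0.2 it is 0.4 × 0.05 = 0.020. The ratios are again 3 and 1.5.

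**Step 2: counselling time.** 3 calls × 1 h = 3 h per intervention dyad. The number of dyads per arm is not in the text. Four centres at 24% imply 4/0.24 = 16.7, that is 17 of 34 centres, so an even split of dyads is a reasonable assumption: 453/2 × 3 h = 679.5 h, roughly 680 h. At the assumed rates this is EUR 90 to 300 per dyad, or about EUR 20,000 to 68,000 in all, before counsellor training, supervision and call preparation.

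**The case against.** The strongest defence is that the article says openly what it is doing. The sentence ties the calculation to time remaining at home, which matches hypothesis iii, and it does not say that this is the only QALY to be computed. The first part stands: the measure is coherent as quality-weighted home time. It does not rescue the plan, because the quantity is named a QALY and is the only one described for users.

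A reader might infer that the rule favours the intervention. The documents do not support that. It applies to both arms, changes nothing if admission times are equal, and counts against the intervention if admission comes earlier (−0.049 v −0.016 above). It overstates the gain only if admission is delayed.

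A reader might also expect the rule to distort the budget impact analysis. That analysis concerns health-system expenses, and QALYs do not enter it.

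On size, the inflation factor is unknown because the article gives no utilities. A six-fold figure follows from 0.6 at home and 0.5 in a nursing home (0.6/0.1), but the 0.1 decrement would be purely an assumption.

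Finally, a reader might infer that the counselling is to be treated as free. The cost sentence says that costs include certain items, which can be an open list, and a journal article commonly leaves detailed costing to a fuller plan. That objection largely stands, which is why the cost point is secondary. What remains is that the list goes down to handbooks and yet does not name one of the two intervention components.

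**Conclusion.** The zero rule is a stated rule, not a detail left to another document, and followed as written it does not yield a QALY. It multiplies the admission-timing part of the QALY difference by 1.5 to 3 for utilities of 0.6 at home and 0.2 to 0.4 in a nursing home, and by 1.4 to 5 when the at-home value is varied from 0.5 to 0.7. The factor grows without limit as the two utilities converge. Differences in utility while users are still at home are not affected. These figures rest on assumed utilities and equal survival; the direction depends on which arm stays at home longer.

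The counselling point is a request for clarity: about 3 counsellor hours per intervention dyad are not named as a cost. If they were in fact left out, only intervention-arm cost would fall, whatever the trial's result. The hours have not been set against total costs, so their weight in the cost difference is not known.

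Neither point touches the four primary outcomes. Both should be corrected before the cost-utility result is used.

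**What to change.** In the base-case QALY, set the user's utility to 0 only from death. Value nursing-home time with the EQ-5D-5L where it is collected after admission. The caregiver interviews at 6, 12 and 24 months cover the user's situation by observer rating, and the stated barrier to follow-up after transfer concerns tests done at the centres. Whether the user's EQ-5D-5L is still obtained after admission cannot be seen, because the content of Table 5 is not shown. Where it is not available, impute a value that allows for a change on admission and vary it in sensitivity analysis. Carrying the last at-home value forward would assume that admission has no effect on quality of life and would bias the result the other way. Report the present rule separately, labelled as quality-weighted time at home.

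State counsellor call time, training and supervision as intervention costs.

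The price is a little more analysis, some costing from the project's own records, and a cost-utility result that may look less favourable.

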## Discussion

In this article, we describe the design of a large cluster-randomised, controlled study on the effects of a multicomponent intervention for people with cognitive impairment carried out at day-care centres. The effects on the users’ informal caregivers who receive a brief telephone intervention are also investigated.

Two conditions must be fulfilled to allow people with cognitive impairment to remain at home, which is desirable from both an economic perspective and the perspectives of the people with cognitive impairment and their caregivers. People with cognitive impairment need to sustain their cognitive capacities and their abilities to perform activities of daily living at as high a level as possible [9]. Their informal caregivers need to learn how to deal with the situation in a helpful way so as to keep their physical and mental burden as low as possible [10, 18]. This study addresses both of these conditions, first by providing an evaluated multimodal intervention for day-care centre users and second by supporting their caregivers through counselling that is oriented specifically towards caring for people with cognitive impairment.

The day-care centres have the advantage that they are in a position to combine two helpful approaches. Time is freed up for the caregivers, and the people with cognitive impairment can be offered an effective, non-drug group treatment.

### Strengths and limitations of the study design

Strengths of the study design are the cluster randomisation, the long follow-up period of 2 years, the use of a manualised treatment that has already been evaluated in nursing homes [15, 16, 22], the naturalistic setting in care institutions which are already part of the German health care system, and the focus on the dyad consisting of both the person with cognitive impairment and his/her informal caregiver.

Moreover, due to the recruitment of day-care centres throughout Germany and the balanced ratio of urban to rural day-care centres run by a wide variety of organisations (local authorities, non-profit, and private), the external validity of the study is high. The naturalistic design – in which the study has no influence on the number of days the people with cognitive impairment attend the day-care centres (days of treatment in the intervention group) – also makes it possible to analyse subgroups in order to determine the necessary intensity of the treatment.

We decided on cluster randomisation rather than randomisation on the participant level for two reasons. If two groups that are separate in terms of rooms and staff – one treatment group and one control group – were to take place at the same day-care centre, only a very few very large day-care centres would have the necessary capacity. These day-care centres are not representative of the general healthcare situation and would thus markedly reduce the external validity. In addition, implementing two study groups simultaneously in the same institution would be associated with a risk of halo effects by which the treatment might influence the control group.

The possible disadvantage of a systematic difference between the arms of the study arising by chance from the cluster randomisation is offset both by the large number of 34 randomised day-care centres and by the stratification by region [51].

Overall, it can be assumed that the control group consists of day-care centres that tend to be quite active and not only accept the extra work involved in the study but also receive the study-specific therapy 6 months after baseline. Differences between the groups will therefore tend to be under-estimated rather than over-estimated. Since the study requires extra work by the day-care centres, offering the treatment to the control group is necessary to motivate them to participate in the study in the first place. As the control group was also trained in the MAKS treatment after a delay of 6 months but did not get the supervision that the intervention group did, important hints for implementation can be drawn from the comparison between the two “intervention” phases, that is, between the regular, controlled intervention phase in the intervention group during the first 6 months and the less structured, independent implementation in the control group, which begins after 6 months of waiting.

In order to be able to replicate and implement any treatment, a good manual is needed, particularly in the case of non-drug therapies [52]. For the MAKS therapy, in particular, this is ensured by the compilation of 125 structured days of therapy in the 6-month controlled intervention phase. For each day of the study, the contents of each of the four MAKS components are carried out as stated in the study manual by all day-care centres. A manual was also created for the intervention for the caregivers. This makes both treatments easy to implement because only one training is required, and thus the necessary personnel and space are usually present on site.

One basic problem with non-drug therapies is the fact that they cannot usually be blinded. We try to protect the collection of the data on the primary outcomes for the day-care centre users as much as possible from a data collection bias. The trained testers are not allowed to be involved in the care of the day-care centre users and have to come from outside the centres to carry out their tasks.

As far as we know, this is the first time that the effectiveness of an evaluated non-drug therapy has been tested in people with cognitive impairment (including some with diagnosed dementia) in combination with outreach counselling for their caregivers in a sample in a real healthcare environment.

## Abbreviations

ADL: Activities of daily living
BIZA-D: Berlin Inventory of caregivers’ burden with dementia patients
BSFC-s: Burden Scale for Family Caregivers short
CATI: Computer-assisted telephone interview
DeTaMAKS: a cluster-randomised, controlled intervention study examining MAKS therapy for people with cognitive impairment in day-care centres
EQ-5D-5L: EuroQol five dimensions questionnaire
ETAM: Erlangen test of activities of daily living in people with mild dementia or mild cognitive impairment
FIMA: Questionnaire for the use of medical and non-medical services in old age
IADL: Instrumental activities of daily living
ICF: International Classification of Functioning, Disability, and Health
MAKS: Multicomponent group therapy for people with cognitive impairment (motor stimulation, activities of daily living and cognitive stimulation in a social setting)
MMSE: Mini-mental state examination
MoCA: Montreal Cognitive Assessment
NOSGER: Nurses’ Observation Scale for Geriatric Patients
NPI-Q: Neuropsychiatric Inventory-Questionnaire
RUD: Resource Utilization in Dementia
WHO-5: Well-Being Index
